##### Interim analyses {21b}

In the design of this study, no interim analyses are planned.

### Methods for additional analyses (e.g., subgroup analyses) {20b}

No additional analyses not described in Section 20a are planned.

### Methods in analysis to handle protocol non-adherence and any statistical methods to handle missing data {20c}

In this study, we will prioritize the utilization of data provided by participants who discontinue their involvement before the final follow-up. Any incomplete data as a result of participant withdrawal will be categorized as missing, and estimation or imputation methods will not be employed for these missing values.

### Plans to give access to the full protocol, participant-level data, and statistical code {31c}

Fully anonymized data and statistical codes will be made available in public databases after completion of the trial.

### Oversight and monitoring

#### Composition of the coordinating center and trial steering committee {5d}

The steering committee for this study consists of the principal investigator and two co-investigators who are responsible for overseeing the implementation of the study. Coinvestigators who are graduate students in the field of endocrinology will be involved in patient recruitment, obtaining informed consent, and follow-up. The principal investigator will independently generate a random allocation sequence and assign the participants to the two intervention groups. Additionally, the steering committee has the authority to review and approve necessary modifications to the study protocol.

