### Trial design {8}

This randomized, controlled, double-blind pilot trial will be conducted in Chengdu, China. Eligible participants will be randomly allocated to two parallel groups (1:1 ratio). All participants will retain the right to withdraw at any stage, consistent with the Standard Protocol Items: Recommendations for Interventional Trials (SPIRIT) guidelines (23). **Figure 1** presents a flowchart of the study.

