### Relevant concomitant care permitted or prohibited during the trial {11d}

Throughout the study, foundational treatment will be emphasized for patients with diabetes. Participants are permitted to continue their pre-existing, stable (≥4 weeks of use prior to enrollment) conventional glucose-lowering medications—including metformin, sulfonylureas, sodium-glucose cotransporter-2 inhibitors, insulin and its analogues—in addition to the investigational product (liraglutide or placebo), in order to comply with ethical standards and maintain glycemic stability, while the initiation or switch to dipeptidyl peptidase-4 inhibitors, other GLP-1 receptor agonists, and related preparations is strictly prohibited. To ensure comparability of background therapy between groups, we will implement stratified randomization based on baseline insulin use and will meticulously record and compare all baseline glucose-lowering medications across groups prior to analysis to confirm randomization balance.

For the basic treatment protocol, the study will adhere to the recommendations outlined in the Chinese Diabetes Prevention and Treatment Guidelines (2020 edition).

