### Assignment of interventions: allocation

#### Sequence generation {16a}

After obtaining informed consent and post-baseline assessments, researchers will be alerted to initiate the group allocation process. Participants will be randomly assigned to one of the two groups at a 1:1 ratio using a system of generated random numbers. These numbers will be stored in opaque sealed envelopes, from which each participant will randomly selected one, thereby determining their allocation to either the treatment or control group. Patients will be evenly distributed between two interventions: once-daily administration of placebo in a blinded manner and once-daily liraglutide in a blinded manner. The hospital’s central pharmacy will be responsible for dispensing both placebo and the active drug. To maintain the integrity of the double-blind protocol, participants, researchers, and study monitors will not be privy to treatment assignments within the placebo and liraglutide groups at any time.

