#### Concealment mechanism {16b}

Liraglutide and its placebo will be manufactured to be identical in appearance to ensure that the participants are blinded to the assigned medication. Sealed envelopes, each corresponding to a participant and containing details of the randomization sequence, will be stored securely to ensure that they are not accessible to the researchers at any time, thus preserving the integrity of the double-blind study design.

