#### Implementation {16c}

The randomization procedure will be implemented using a web-based randomization system provided by the Chinese Clinical Trial Registry (http://www.medresman.org.cn/login.aspx).

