### Assignment of interventions: blinding

#### Who will be blinded {17a}

A triple-blind design will be rigorously maintained throughout the trial period, encompassing all participants, healthcare personnel, and investigative staff from initial enrollment through the terminal follow-up assessment. Systematic disclosure of treatment allocations shall be deferred until study completion for all enrollees and conclusive verification of analytical results has been achieved.

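### Allocation is described in conflicting ways, one of which has the principal investigator generate the sequence and assign participants; the promised insulin stratification appears in none of them, so concealment and blinding are not assured

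*Protocol article*

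**What the plan says.** Five sections of the protocol article bear on how a participant reaches an arm.

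- Sequence generation {16a}: "These numbers will be stored in opaque sealed envelopes, from which each participant will randomly selected one", and the draw fixes the arm. The same section has the central pharmacy dispense both products and says that participants, researchers and monitors do not learn assignments at any time.
- Concealment mechanism {16b}: "Sealed envelopes, each corresponding to a participant and containing details of the randomization sequence, will be stored securely". Researchers are never to have access to these envelopes. Active drug and placebo look the same.
- Implementation {16c}: "The randomization procedure will be implemented using a web-based randomization system provided by the Chinese Clinical Trial Registry".
- Composition of the coordinating center and trial steering committee {5d}: "The principal investigator will independently generate a random allocation sequence and assign the participants to the two intervention groups".
- Relevant concomitant care {11d}: "we will implement stratified randomization based on baseline insulin use", so that background therapy is comparable between arms.

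On blinding, Who will be blinded {17a} states: "A triple-blind design will be rigorously maintained throughout the trial period". It includes investigative staff, from enrolment to the last follow-up. Procedure for unblinding {17b} has the trial pharmacy keep the randomization code and makes the principal investigator responsible for the causality assessment of serious adverse events. Adverse event reporting {22} adds an independent Safety Monitoring Board that reviews those events separately.

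**The concern.** Site staff cannot carry out all of these instructions at once, and the choice between them decides whether allocation is concealed. If the person who leads the trial makes the list and places participants in groups, that person may know the next allocation and every past one. Section {5d} puts the same person on a three-member steering committee with two co-investigators, and gives recruitment, consent and follow-up to co-investigators. Knowledge of the sequence would thus sit close to the people who enrol. It would also sit with the person who first judges whether a serious adverse event is related to treatment. HAMD, listed among the primary outcomes, is scored by raters, so leaked allocations could affect it.

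The second issue is stratification. It is promised in a section on concomitant care but not carried into any section that describes allocation. If the envelope draw is what happens in practice, the promised balance in insulin use is not delivered by design.

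**Working it through.** **Step 1. Set the accounts side by side.**

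| Section | What decides the arm | Who holds or may see the sequence |
|---|---|---|
| {16a} | Participant's own draw from envelopes | Researchers and monitors not told assignments |
| {16b} | Envelope already tied to that participant | No researcher access at any time |
| {16c} | Web-based system | Not stated |
| {5d} | Principal investigator assigns | Principal investigator generates it |
| {17a} | – | Investigative staff blinded throughout |
| {17b} | – | Code kept by the trial pharmacy |

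**Step 2. Sort the pairs.**

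- Firm conflict: {16a} against {16b}. A free choice among envelopes cannot decide the arm if each envelope is already matched to a person.
- Firm conflict: {16a} against {5d}. The participant's draw and the principal investigator's assignment cannot both decide the arm.
- Firm conflict on a literal reading: {5d} against {16b}, and against the blinding statements in {16a} and {17a}. The principal investigator is a researcher, and someone who generates a sequence has had access to it.
- Reconcilable: {16c} with the others. A web system could produce the list that fills the envelopes, or be the tool that the principal investigator operates.

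**Step 3. Check stratification.** {11d} names one stratum variable, baseline insulin use. {16a}, {16b}, {16c} and {5d} name none. A web system could carry strata, so the silence of {16c} is an omission. A single pool from which each participant takes any envelope cannot carry them, so {16a} as written conflicts with {11d}.

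**Step 4. Size of the imbalance if the free draw were used.**

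Inputs: about 60 participants, 30 per arm (Sample size {14}). This figure reproduces from the article's own minimum of 25 per group and its upper dropout bound of 15%: 25 / (1 − 0.15) = 29.4, rounded up to 30 per arm. The number of insulin users, K, is not given; 10, 20 and 30 are assumed.

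Model: with one pool of 30 active and 30 placebo envelopes, the number X of insulin users in the liraglutide arm is hypergeometric,

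P(X = x) = C(K, x) · C(60 − K, 30 − x) / C(60, 30).

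The between-arm difference is |X − (K − X)| = |2X − K|.

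For K = 20, a difference of 4 or more means X ≤ 8 or X ≥ 12, that is, a split of 12 v 8 or worse. P(X ≤ 8) = 0.206, and by symmetry the total is 2 × 0.206 = 0.412. A split of 13 v 7 or worse has probability 2 × 0.085 = 0.170.

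| Assumed insulin users K | P(difference ≥ 4) | P(difference ≥ 6) |
|---|---|---|
| 10 | 0.299 | 0.080 |
| 20 | 0.412 | 0.170 |
| 30 | 0.439 | 0.196 |

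These are chances of imbalance only. They are not an estimate of bias in HAMD, HbA1c or any other outcome.

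**The case against.** The strongest reply is that the article already states several protections. The central pharmacy dispenses, the products look alike, the envelopes are kept from researchers and the trial pharmacy holds the code. A list of coded kits released to the pharmacy would satisfy all of these and leave the principal investigator blind even after producing the list. The troublesome sentence stands in a section on committee composition and may be loose wording. No section makes the principal investigator a HAMD rater, and the Safety Monitoring Board gives a second, independent view on every serious adverse event. Strata and blocks are details that a condensed article may leave to the full protocol, and {11d} also plans to record and compare background glucose-lowering drugs.

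Much of this stands. A reader might infer that concealment and blinding fail, or that all 60 allocations will be known to the principal investigator. The article does not support that: it follows only from the most literal reading of {5d}, and it leaves out the stated safeguards. Nor are all the accounts mutually incompatible, since the web system can coexist with either envelopes or an operator. It would also be too strong to say that the protection against insulin imbalance does not exist; only the single-pool draw defeats it.

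The reply does not remove the point. The article describes no coded-kit arrangement, and {5d} speaks of assignment to the intervention groups, not to kit numbers. Pharmacy custody of a code does not blind whoever generated it. Safety board review does not protect enrolment or HAMD rating. The conflicts identified as firm in the working are between statements in the text, not gaps that a fuller document would fill.

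**Conclusion.** The point holds as an internal contradiction that should be resolved before enrolment, because allocation cannot be repaired afterwards. The sections disagree on what decides the arm and on who may hold the sequence. Read literally, the principal investigator's role in {5d} contradicts {16a}, {16b} and {17a}. Concealment and blinding are therefore not assured; the text does not show that they are lost.

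Stratification by insulin use is promised but absent from the allocation sections, and the envelope draw in {16a} could not deliver it. The size given for that, a chance of about 30% to 44% of a difference of 4 or more insulin users, rests on three assumptions: the single-pool draw is actually used, the arms are exactly 30 and 30, and there are between 10 and 30 insulin users. The contradictions themselves depend on none of these figures.

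**What to change.** State one mechanism, and state it the same way in {5d}, {11d}, {16a}, {16b} and {16c}.

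1. Keep the web-based system of {16c}, with a list stratified by baseline insulin use.
2. Name a person or unit independent of enrolment, outcome assessment and causality judgement to generate the list. The central pharmacy, which already dispenses, is one possibility. Release the list only to that pharmacy.
3. Delete the participant envelope draw from {16a} and {16b}. Pharmacy-held codes for emergency unblinding may stay, in line with {17b}.
4. Delete the principal investigator's generating and assigning role from {5d}.

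The cost is protocol wording, set-up of two strata and naming the generator. No added visits or participants are needed. The article does not say whether the chosen system supports stratification and pharmacy-only release, so confirm both first.

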#### Composition of the data monitoring committee, its role and reporting structure {21a}

Due to the simplicity of the study, a data monitoring committee is not required.

#### Adverse event reporting and harms {22}

Adverse events will be stringently monitored. The recruiting physician will oversee the management of these events. When a patient encounters an adverse event, assessors, therapists, or other personnel will provide immediate emergency care and notify the recruiting physician. The recruiting physician will then be tasked with reporting adverse events to the principal investigator and ethics committee. The principal investigator is responsible for thoroughly informing the ethics committee about the adverse events, including their contexts and relevant details. Additionally, the recruiting physician must ensure that all adverse events are meticulously recorded in the Clinical Report Form to maintain accurate documentation.

Furthermore, given the psychiatric risks in the study population, an independent Safety Monitoring Board (SMB) will be established to conduct periodic safety reviews. The SMB will consist of independent experts not involved in trial conduct. Its key responsibilities include: conducting regular meetings (at least every 3 months) to review all adverse events, with particular attention to psychiatric events (e.g., worsening depression, suicidal ideation) and assessing their relationship to the intervention; being empowered to provide independent recommendations to the principal investigator and ethics committee regarding trial continuation, modification, or termination based on safety evaluations; and performing expedited review and independent assessment of all serious adverse events.

#### Frequency and plans for auditing trial conduct {23}

The research team is expected to deliver a monthly progress update by the conclusion of each calendar month. This document will present a systematic evaluation of the ongoing investigative work while maintaining confidentiality regarding the empirical findings. The key components will include (1) achievement milestones relative to predetermined research goals, (2) status assessment comparing actual progress with projected timelines outlined in the original protocol, and (3) strategic recommendations for plan optimization based on emerging challenges or opportunities identified during implementation.

## Dissemination plans

The results of this study will be published in a peer-reviewed academic journal. Additionally, we intend to present the findings of this study at academic conferences at local, national, and international levels.

### Patient and public involvement

This study was conducted without direct participation from patient representatives or community members in its design phase. The research outcomes will be disseminated through established academic channels including peer-reviewed publications and scientific conferences, adhering to standard research dissemination protocols.

## Discussion

GLP-1RAs, known for their unique blood glucose-lowering and weight-reducing effects, have emerged as a new frontier in the treatment of diabetes and obesity, earning the distinction of being named one of Science magazine’s Breakthroughs of the Year 2023. These agents may have revolutionary applications in the treatment of mental health problems and neurodegenerative diseases (35).GLP-1RAs, beyond their established role in improving insulin resistance (36), may have therapeutic potential for mental health disorders, such as depression and bipolar disorder, as well as for neurodegenerative diseases associated with cognitive dysfunction, including Parkinson’s and Alzheimer’s diseases (37, 38). Recent animal studies suggested that semaglutide has the potential to combat depression and anxiety. Mice with depression associated with type 2 diabetes induced by a high-fat diet showed a significant alleviation of depressive and anxiety-like behaviors following treatment with semaglutide, along with enhanced cognitive function (39). In a clinical trial focusing on obese patients with type 2 diabetes or prediabetes, liraglutide mitigated early cognitive dysfunction in individuals with diabetes (40). However, several potential adverse effects associated with GLP-1RAs warrant careful consideration. One study suggested that individuals taking semaglutide may be at a disproportionately higher risk of suicidal thoughts, with a 45% increased risk compared with those taking other medications. Moreover, this risk was quadrupled in patients who concurrently used semaglutide and antidepressants. In contrast, the use of liraglutide alone was not associated with an increased risk of suicidal ideation (41). A retrospective cohort study published in Nature Medicine, which included the health records of over one million patients, suggested that GLP-1RAs are associated with a lower risk of suicidal ideation compared to other types of obesity and diabetes therapies; therefore, approaching these findings with caution and continuing to monitor for potential adverse effects are necessary (42). Some experts recommend caution when using GLP-1RAs in patients with a history or risk of mental illness, emphasizing the need for close monitoring of their emotional states. Therefore, this study will include patients with mild-to-moderate depressive symptoms to ensure close monitoring of mood changes throughout the trial and subsequent follow-ups.

Limitations of this study must be acknowledged: 1) The intervention duration of 12 weeks is relatively short, thus limiting the evaluation of the long-term efficacy (including whether improvements in metabolism and depressive symptoms can be sustained) and long-term safety profile of liraglutide; 2) The findings are derived from a single-center Chinese population and require validation in multicenter studies and non-Chinese populations. Considering these limitations, future definitive studies should significantly extend the observation period (e.g., to 6 months or longer) to comprehensively assess the durability of efficacy, long-term safety, and potential delayed effects.

## Data Availability

The original contributions presented in the study are included in the article/Supplementary Material. Further inquiries can be directed to the corresponding authors.
